#### **Data collection techniques, participant tasks and time involved**

Monitoring of weekly daytime breastfeeds will not require extra time for the mother or infant and will last from 15 to 60 minutes depending upon the feed duration. The following data collection techniques are used:

##### **Intra-oral vacuum**

Intra-oral vacuum (relative to atmospheric, mmHg) will be measured via a small Silastic tube (SNS, Medela AG, Baar, Switzerland) attached to a pressure transducer (Cobe Laboratories, Frenchs Forest, NSW, Australia) taped alongside and terminating just past the nipple tip (2mm). The pressure transducer will be connected to a bridge amp (AD Instruments, Castle Hill, NSW, Australia) via an interconnect cable (Cobe Laboratories). The output of the pressure transducer and ultrasound images will be channeled to a Power Lab (ADInstruments, Castle Hill, NSW, Australia) and simultaneous recordings made using the software package Chart v4.5 (AD Instruments) on a laptop computer. The Silastic tube is very fine and soft; very young infants do not appear to be aware of the presence of the tube and its presence does not cause any discomfort to the breastfeeding mother.

##### **Ultrasound Imaging**

Submental mid-sagittal scans of the infant's oral cavity will be performed for the duration of the entire feed. The infants will be scanned using a Sonologic SonoScape (Brisbane, Australia) with a 5PI phased array transducer and Parker Ultrasonic Gel (Fairfield, New Jersey, USA). Two focal zones will be employed to narrow the ultrasound beam and improve image resolution. One will be located at the level of the hard palate and the other at the nipple-tongue border. All scans will be channeled into the Power Lab and recorded for later analysis.

### **Respiration and swallowing measurements**

Patterns of infant respiration and swallowing will be measured using respiratory inductive plethysmography (RIP), (Respirace QDC, SensorMedics, Yorba Linda, CA, USA) with two bands; one placed around the thorax at the level of the nipples and a second around the abdomen at the level of the umbilicus. Bands will be secured using Micropore tape if necessary. The bands are connected to the Respirace and channeled into the Power Lab. RIP has been validated against ultrasound as a highly reliable method for identifying swallows during breastfeeding [7] and has been used successfully to compare respiratory changes for breast and bottle-feeding in term infants [8].

### **Oxygen saturation and heart rate monitoring**

Oxygen saturation and heart rate monitoring will be performed for the duration of the test feeds. (As per SCN policy all infants <34/40 are continuously monitored). For infants no longer requiring monitoring, pulse oximetry will be used for monitored feeds, with a sensor attached to the infants' foot. The research nurse will record any episodes of oxygen desaturation and bradycardia during the feed. These events will be documented on the intraoral vacuum and respiratory traces to enable retrospective identification of the episodes.

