### Trial Aims

1. To track maturation of intraoral vacuum and SSB coordination as well as physiological stability of breastfeeding preterm infants over time and determine if this is related to increased effectiveness and efficiency of breastfeeding. We hypothesize that improvement in breastfeeding efficiency (mL/min) and effectiveness (total mL transferred) will be associated with changes in one or more of vacuum strength (average and changes across a feed), consistency of sucking (number of sucks/suck bursts per feed) and SSB coordination.
2. To explore the effect of the volume of milk in the breast on milk transfer during breastfeeding at 34 weeks CGA. Our hypothesis is that more milk in the breast will result in a higher volume of milk being transferred by the infant at the breastfeed.
3. (Optional) To explore the effect of nipple shield use on milk transfer at 35 weeks CGA. The hypothesis is that nipple shields improve attachment and breastmilk transfer
2. To compare SSB coordination and maturation during breastfeeding with bottle feeding with a Calmita teat, and bottle-feeding with a conventional teat. Our hypothesis is that infants fed with a Calmita teat will experience less apnoea and bradycardia and reach full oral feeds more rapidly than those fed with a standard teat.
3. To determine the effect of a vacuum triggered teat (Calmita during stay in study hospital, and Calma used for top up feeds post discharge/transfer from the study hospital) on the timing of achievement of full breastfeeding and on breastfeeding duration.

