### Trial Design

#### Trial endpoints

The primary endpoint for this trial is total breastfeed volume (mL) transferred at a breastfeed, measured at 33, 34, 35 weeks and term CGA

Secondary endpoints to be measured during monitored feeds are  
efficiency (mL/min)

- total suck duration

- total suck bursts
- mean, peak and baseline intraoral vacuum (mmHg)
- oxygen saturation range
- heart rate range
- incidence of bradycardia
- incidence of oxygen desaturation

The following feeding endpoints will also be determined

- timing of achievement of full oral feeds
- timing of achievement of full breastfeeding
- breastfeeding duration (monitored up to 3 months post-term)

1. A randomized controlled clinical trial will be undertaken with random allocation in blocks of size 4 to either a control group or an intervention group. Study design is depicted in Figure 1.
2. A pilot study of up to 5 infants will be completed prior to commencement of the trial to test and refine the set-up and duration of monitoring sessions.
3. Study participant data and milk samples will be re-identifiable, with an identification code assigned to each infant. A master sheet that matches infant identity to identification codes will be stored in a password-protected electronic file on a lap top computer. All paper copies of case report forms will be stored in a locked filing cabinet at The University of Western Australia.
4. The effect of a vacuum-controlled bottle-feeding teat (Calmita and Calma teats, Medela AG) on breastfeeding outcomes will be evaluated in this clinical trial. A shut-off valve is incorporated into the Calmita teat so milk flows only when the infant creates a vacuum. Venting prevents collapse of the teat. There are two versions of Calmita with different threshold levels for the vacuum-controlled valve of  $-10 \pm 5$  mmHg (starter teat) and  $-30 \pm 15$  mmHg (advanced teat). We have previously investigated a prototype of this product but wish to carry out more extensive studies on the final product.

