## Treatment of Participants

1. When the mother is not available to breastfeed, control group infants will use a conventional teat for suck feeds whereas the interventional group infants will use the Calmita teat. The starter teat will be offered initially and when the infant takes full feeds from the starter teat for 48-72 hours they will then use the advanced teat.
2. Monitoring of a weekly breastfeeds and bottle feeds with the allocated teat will be performed at 33, 34 and 35 weeks CGA and involves the following
  - Weigh infant pre and post breastfeeding
  - Intraoral ultrasound
  - Continuous Intraoral vacuum measurements
  - Respiratory Inductive plethysmography
  - Continuous pulse oximetry for oxygen saturation (SaO2) and heart rate
  - (optional) Maternal pre/post breastfeed milk samples <1.0mL
  - Maternal rating of Preterm Infant Breastfeeding Behavior Scale[5] (PIBBS, Appendix A)

SSB coordination is evaluated using data from intraoral vacuum, respiration and swallowing (Respiratory Inductive Plethysmography) heart rate and oxygen saturation obtained throughout the entire breastfeed[6].

3. Test weights of the infant pre and post feed, for all feeds, will be made to determine milk intake and allow calculation of top up feeds. For monitored feeds, pre and post feed milk samples (<1.0mL) will be collected and fat content measured to provide a further estimate of breast fullness.
4. At each monitored breastfeed the Preterm Infant Breastfeeding Behavior Scale[5] (PIBBS, Appendix A) will be completed by the mother.
5. In the study setting it is assumed that most stable preterm infants are offered (at least daily) breastfeeding experiences from 32 weeks CGA. A weekly breastfeed will be monitored from 33 weeks CGA. At 34 weeks CGA each infant will have up to 2 breastfeeds and one bottle-feed monitored in random order on 2-3 consecutive days with a full or empty breast. A full breast is one that has not been expressed for 3 hours prior to feeding and an empty breast one that has been expressed within an hour of the feed. At 35 weeks CGA those using a nipple shield will have the option of also having a monitored breastfeed without a nipple shield.
6. At 35 weeks or at discharge/transfer each infant will have 1 breastfeed monitored with or without a nipple shield depending on whether the infant is typically feeding with a shield, and one bottle-feed will be monitored. Infants

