### Bottle feed

☐ Calmita starter    ☐ Calmita advanced                      ☐ Conventional

Pre feed weight:                      Pre feed milk sample                      ☐

Post feed weight:                      Post feed milk sample                      ☐

Total volume transferred:

Heart rate range:

SaO2 range:

☐ Resp plethysmography

☐ Intraoral vacuum

☐ PIBBS completed by mother

PIBBS score: \_\_\_\_\_

☐ 24hr production and milk samples collected    Result \_\_\_\_\_mL

Total number of feeds in last 7 days: \_\_\_\_\_

Total number of oral feeds: \_\_\_\_\_

Of these, total breastfeeds: \_\_\_\_\_

**Adverse events** – details eg. bradycardia, apnoea, interventions required

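### Bradycardia and desaturation are counted from a live nurse call, with no written criterion and no masking described, although oximetry runs continuously: derive them from logged signals by one rule

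*Combined protocol and SAP*

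**What the plan says.** - **Endpoints.** The secondary list under Trial endpoints includes "incidence of bradycardia" and "incidence of oxygen desaturation". It also lists heart-rate range and saturation range. Apnoea is not on that list, but Assessment of Efficacy and Assessment of Safety both name it with bradycardia.
- **Hypothesis.** Trial Aims predicts that "infants fed with a Calmita teat will experience less apnoea and bradycardia". Desaturation is not part of that prediction.
- **Method.** Oxygen saturation and heart rate monitoring says: "The research nurse will record any episodes of oxygen desaturation and bradycardia during the feed". It continues: "These events will be documented on the intraoral vacuum and respiratory traces to enable retrospective identification of the episodes".
- **Signals.** Treatment of Participants lists "Continuous pulse oximetry for oxygen saturation" and heart rate at monitored feeds. Vacuum, ultrasound and respiratory plethysmography are sent to a Power Lab. The ultrasound scans are "recorded for later analysis"; no matching statement covers the oximeter output.
- **Form.** Appendix E has tick boxes for the teat type, fields for the heart-rate and saturation ranges, and an adverse-event line that prompts for "details eg. bradycardia, apnoea, interventions required". It has no count and no yes/no field for any event.
- **Masking and criteria.** No masking of staff, assessors or analysts is described. No heart-rate, saturation or duration criterion appears anywhere. The reference to events needing intervention, under Criteria for termination of the trial, triggers review of one infant's participation and does not define an endpoint.

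**The concern.** The arms differ by a device that anyone at a bottle feed can see, and the protocol states in advance which arm should have fewer apnoeas and bradycardias. An observer who knows the teat and has no written threshold may call borderline episodes differently in the two arms. Any such difference would show up as a treatment effect or hide one. A mixed model cannot remove it, because the error lies in the recorded outcome.

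The consequences go beyond a secondary comparison. Assessment of Safety sends the apnoea and bradycardia records to the interim review at 15 infants per group, and Criteria for termination of the trial allows that review to halt the trial. Under-recording in either arm would weaken that oversight.

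Writing down a definition would solve only half of this. A threshold applied live by someone who sees the teat is still an unmasked call, and the equipment for a better method is already attached to the infant.

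**Working it through.** **No figure in the plan bears on this point.** The sample-size section expresses detectable differences in secondary outcomes in SD units (0.83 SD), which does not apply to event incidence. It gives no event rate. The only inputs taken from it are the planned numbers: 24 evaluable infants per arm, and 24 / (1 − 0.20) = 30 recruited.

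**Step 1: what each record can show.**
- *The nurse's call* gives episodes she noticed and judged to qualify, with no stated rule.
- *Marks on the traces* help locate episodes that were called. No step is described for finding episodes that were not.
- *The free-text line* cannot distinguish a feed with no event from a feed with nothing written down.
- *The heart-rate and saturation ranges* show the lowest value in the feed. They give neither the number nor the duration of episodes, and nothing about apnoea.
- *Continuous oximetry and plethysmography* could support a count under one rule for all feeds, provided the oximeter output is stored. No such count is planned.

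**Step 2: size, by assumption only.** Let the true infant-level risk p be the same in both arms, with detection s_C (conventional) and s_T (Calmita). The apparent risks are p × s_C and p × s_T, so the apparent ratio is s_T / s_C whatever p is:
- 0.90 / 0.95 = 0.95
- 0.75 / 0.90 = 0.83
- 0.70 / 0.90 = 0.78
- 0.50 / 0.90 = 0.56

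**Step 3: chance of a false finding for Calmita.** With n = 24 per arm, let x ~ Bin(24, p·s_C) and y ~ Bin(24, p·s_T). Sum the joint probabilities over all pairs (x, y) for which the pooled statistic z = [(x − y)/24] / √[p̄(1 − p̄)·2/24], with p̄ = (x + y)/48, exceeds the two-sided 0.05 critical value.

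| True risk, both arms | Detection, conventional / Calmita | Apparent risks | Chance of false finding for Calmita |
|---|---|---|---|
| 20% | 90% / 90% | 18% / 18% | 2.7% |
| 20% | 90% / 70% | 18% / 14% | 5.9% |
| 20% | 90% / 50% | 18% / 10% | 12.5% |
| 40% | 90% / 90% | 36% / 36% | 2.6% |
| 40% | 90% / 70% | 36% / 28% | 8.7% |
| 40% | 90% / 50% | 36% / 20% | 23.8% |
| 60% | 90% / 90% | 54% / 54% | 2.9% |
| 60% | 90% / 70% | 54% / 42% | 14.6% |
| 60% | 90% / 50% | 54% / 30% | 41.8% |

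With 30 per arm, the 90% / 70% rows become 6.2%, 9.4% and 15.5%. The test is symmetric, so swapping the detection rates gives the same chances of a false finding against Calmita. The 90% / 50% rows are an extreme case. At the plan's 0.029 level every chance, including those under equal detection, would be smaller.

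**The case against.** The case on the other side has real content.

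- **The ranges are recorded.** A feed's lowest heart rate and saturation give a yes/no event under any later threshold, without the free-text line. This stands as partial mitigation. It does not count episodes, applies no duration, and does not cover apnoea.
- **The match with the hypothesis is partial.** The nurse is assigned desaturation and bradycardia; the hypothesis names apnoea and bradycardia. So the live call covers only one of the two predicted events, and desaturation is affected as a listed endpoint. Apnoea appears on the form's event line, also without a criterion.
- **A stored heart-rate and saturation record is not established.** This stands. Treatment of Participants says these data are obtained throughout the breastfeed for evaluating suck-swallow-breathe coordination, but no section says the oximeter output goes to file. The remedy must therefore include logging.
- **Sight of the teat is inferred.** It follows from the device in use and the absence of any masking text, and it applies to bottle feeds. No teat is in use at breastfeeds, though allocation may be known.
- **The direction is open.** A reader might infer that the bias must favour Calmita. The documents do not support that: the safety review looks for harm from the trial teat, which could equally sharpen vigilance in that arm.

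Two further inferences are tempting. One is that the nurse's marks steer the scoring of the traces. The text is equally consistent with plain time-marking, and nothing says incidence is scored from the traces. The other is that a missed event is analysed as no event. No coding rule for blanks is stated.

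**Conclusion.** The concern holds as a question of method. Two listed secondary endpoints rest on a live call with no criterion and no masking described, while a continuous signal is available at the cotside and no rule-based reading of it is planned. Differential detection between arms is possible. Its size and direction cannot be derived from the documents, and the percentages above depend entirely on the assumed true risks, the assumed detection rates, one yes/no outcome per infant and a 0.05 test.

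It does not follow that the comparison is biased, or that the protocol already holds an objective count and ignores it. The primary endpoint, breastfeed volume by test weighing, is unaffected. This is a worthwhile, low-cost improvement to secondary and safety endpoints and not a threat to the main result.

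**What to change.** 1. State that oximeter output is logged to file for every monitored feed, breast and bottle, on the same time base as the Power Lab channels.
2. Have the investigators prespecify the criteria, including any minimum duration, for bradycardia, desaturation and apnoea. The values are theirs to set.
3. Derive bradycardia and desaturation from the logged oximetry, and apnoea from the plethysmography. Apply one rule to all feeds, from files coded without the arm label.
4. Keep the nurse's log for real-time safety and as a cross-check on the derived events. Add a yes/no field and a count for each event to Appendix E, so that a blank is not ambiguous.

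The cost is data logging, a scoring script, some artefact cleaning and a small form change. Masking may be incomplete where the bottle-feed ultrasound or vacuum trace reveals the teat; scoring the oximetry and plethysmography files separately from those channels limits this.

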### **Infant milk intake**

To determine milk intake infant test weighs will be performed for all breastfeeds. Electronic scales (BabyWeigh Scale, Medela AG, Baar, Switzerland, sensitive to 2 grams) will be used to weigh infants before and immediately after the feed. The amount of milk consumed is calculated as the difference in grams between the pre-feed and post-feed infant weights, and 1gram  $\approx$  1mL. Milk transfer (g/minute) is calculated as the amount of milk consumed during the feed (g) divided by the duration of the feed (minutes). Knowledge of milk intake during a breastfeed will allow for accurate calculation of top up feeds.

### **Estimation of Degree of Breast Fullness**

Breastmilk fat concentrations increase as the volume of milk available within the breast reduces. Changes in breastmilk fat concentration over the course of a breastfeed or expression provide an indication of fullness, and when pre/post samples are collected over a 24hr period, estimation of the degree of fullness can be made [9, 10]. A small milk sample (<1.0mL) will be taken before and after monitored feeds, and mothers will have the option of collecting pre/post samples when recording their 24hr milk production.

### **Preterm Infant Breastfeeding Behavior Scale[5] (PIBBS, Appendix A)**

The PIBBS rates aspects of breastfeeding such as rooting, attachment, sucking and swallowing using a six item scale, with higher scores indicating greater competence. The scale has a reported inter-rater reliability of 0.68 to 0.94. Completion of the PIBBS takes <5 minutes. Mothers will be asked to complete the PIBBS after each monitored breastfeed.

### Assessment of Efficacy

Efficacy of the trial teat will be evaluated through measurement of the primary endpoint ie. total volume transferred at the breast, and secondary endpoints that relate to breastfeeding outcomes (eg. volume transferred per minute, range and average intraoral vacuum, achievement of full oral feeds, full breastfeeding and breastfeeding duration) and safety (eg. SSB coordination and incidence of apnoea and bradycardia during feeding). To assess efficacy, total volume transferred at the breast will be examined at interim analysis when complete data is available for 15 infants in each group, and again on completion of the study.

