**Criteria for termination of the trial:**

Individual participants. Infants that demonstrate physiological instability ie. oxygen desaturations / bradycardia that require intervention (supplemental oxygen, or bag and mask ventilation) during a monitored study feed, where there have been no other episodes in the previous 24 hours, will be referred for review by clinical staff and advice sought re whether the infant should be withdrawn from the trial.

Entire trial: Safety of the trial will be monitored continuously and formally reviewed at interim analysis ie. at recruitment of 15 infants to each arm of the study to determine whether any adverse events have been reported as a result of monitoring or use of the trial teat. In that case, the trial will be stopped while the events are fully investigated, reported to WNHS Ethics Committee, and continuation of the trial re-considered.

We do not anticipate any adverse effects of the vacuum-triggered trial teat as data from our previous study indicates no change in physiological stability during its use of whereby, unlike a conventional teat, milk flow is controlled by the infant during feeding.

5. The expected duration of the trial is 12 months. The total duration of participation of mothers and infants is up to 43 weeks including intermittent monitoring over 3 weeks during hospitalization, one study site visit (likely to coincide with a scheduled hospital follow-up visit) and up to 3 follow up phone calls following discharge from the study site.

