### Statistical analysis, data management, and record keeping

The primary outcome measure for this study is the total volume transferred during a breastfeed. Meier reported average transfer volumes of  $18.4\text{mL} \pm 13.2$  and  $3.9\text{mL} \pm 7.0$  with and without nipple shield, respectively [11]. Samples sizes required to detect a clinically relevant effect of 5mL difference between feeds with full and empty breasts were calculated separately for these two conditions. The more conservative calculation is that the study would need 24 infants in each treatment group to have 80% power (Type I error rate  $\alpha=0.05$ ) of detecting a difference this large. Allowing for a possible dropout rate of 20%, as was observed in a similar study, 30 infants per group will need to be recruited at 33 weeks CGA. The sample size was calculated as if the data will be analysed using an independent samples *t*-test. Actual analyses will be more powerful, and thus will have power to detect smaller differences.

Using this sample size, an independent samples *t* test would have the power to detect differences in secondary outcomes equivalent to  $0.83 * \text{SD}$ . This is equivalent to differences of approximately 3.9 min total sucking duration, and 12 suck bursts per feed. As with the primary outcome, use of covariate data, repeated measurements and more powerful analytic techniques increase the likelihood of detecting smaller differences than those determined here.

Data will be analysed on an intention to treat basis using R 2.15 or later versions (The R Core Team)[12] with nlme,[13] lattice,[14] and multcomp[15] packages for linear mixed models, graphical exploration and general linear hypothesis tests, respectively. To monitor both safety and efficacy, interim analysis will be performed when complete data is available for 15 infants in each group, with p values set to  $p=0.029$  for both interim and final analyses as per Pocock (p372, [16]).

For the monitored breastfeeds, differences in milk transfer volume as well as measured sucking, physiological, and feeding variables, linear mixed effects modelling will be used, with grouping for the random effects at the participant level. Use of nipple shield (yes/no), breast fullness (full/empty) and relevant demographic variables will be considered as predictive factors.

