### **Ethics**

The research nurse ([name], neonatal nurse) or principal research associate ([name], neonatally trained nurse and lactation consultant) will approach mothers of preterm infants that meet the trial criteria. The mothers will be provided with a verbal explanation of the study and will be requested to read the provided written study information sheet. The nurse or associate will offer to return later to find out whether the mother would like to participate with her infant. Any requested additional information will be provided verbally and written consent obtained. (see Appendices B, C for Study Information and Consent forms). The lactation consultants employed by NCCU have been involved in the study design and will support the research nurse, research associate and patients when appropriate.

It is possible that the use of a teat that facilitates the sucking dynamics of a breastfeed may maintain physiological stability as well as provide 'training' that may advance the development of breastfeeding skills, shorten the transition to full breastfeeding, and increase breastfeeding duration. The knowledge gained from the study has the potential to form the basis for evidence-based modification of feeding policies for preterm infants. When initiating breastfeeding for very preterm infants, current advice often includes use a nipple shield to aid attachment, and breast expression prior to offering a breastfeed. There is no/little evidence for this advice. Evaluation of maturation of SSB coordination may also provide markers such as strength of vacuum that are predictive of breastfeeding success. In this case simple monitoring may provide a means for determining readiness for the transition to full breastfeeding.

The coordinating principal investigator (CPI) of the study is also a consultant neonatologist and the Director of the Neonatology Clinical Care Unit (study site). On occasion the CPI may be the assigned neonatologist responsible for the medical care of study participants. The CPI will not be directly involved in recruitment of participants or in data collection. All potential participants will be verbally encouraged to decline or consent freely and voluntarily with assurances that their decision will not impact in any way on their infant's present or future care.

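### The interim efficacy threshold of 0.029 has no stated consequence, and the lower final threshold it brings costs about 5 to 7 points of power

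*Combined protocol and SAP*

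**What the plan says.** All references are to the combined protocol and SAP.

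- *Assessment of Efficacy* makes volume transferred at the breast the primary measure of the trial teat's efficacy. It says that "total volume transferred at the breast will be examined at interim analysis when complete data is available for 15 infants in each group", and again at the end of the study.
- *Statistical analysis, data management, and record keeping* gives the purpose: "To monitor both safety and efficacy, interim analysis will be performed when complete data is available for 15 infants in each group". It sets the threshold, "with p values set to $p=0.029$ for both interim and final analyses as per Pocock". In the same section the sample size is calculated at a type I error of 0.05.
- *Criteria for termination of the trial*, under the entire trial, describes a formal interim review "to determine whether any adverse events have been reported as a result of monitoring or use of the trial teat". The action is tied to that finding: "In that case, the trial will be stopped while the events are fully investigated". Efficacy is not mentioned there.
- *Assessment of Safety* also refers to the interim analysis, for adverse effects only.

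**The concern.** A Pocock level is the price of being allowed to reject at an interim look. The plan writes the price down for both analyses but not what it buys: no section says whether an interim efficacy p-value below 0.029 means stopping, claiming efficacy or continuing.

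Two things are at stake. First, if the plan is followed as written and an interim crossing triggers nothing, the final test runs at 0.029 and the remaining 0.05 − 0.029 = 0.021 of the type I error goes unused. Second, if the interim does cross, the team must choose what to do with the data in hand. At the effect the trial can detect with 80% power, that happens about half the time.

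**Working it through.** **Inputs.** From *Statistical analysis*: 24 analysable infants per arm, 80% power, α = 0.05, an independent-samples t-test for planning, 0.83 SD detectable for secondary outcomes, 5 mL for the primary outcome with SDs of 7.0 and 13.2 mL, and 0.029 at both looks. The interim has 15 infants per arm. Assumptions: two-sided tests (the plan does not say) and an information fraction t between 15/30 = 0.5 and 15/24 = 0.625.

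**1. Reproduce the plan's figures.**
- Pocock level: find α′ such that P(|Z₁| > c or |Z₂| > c) = 0.05, where c is the two-sided critical value for α′ and corr(Z₁, Z₂) = √t. At t = 0.5, α′ = 0.0294, which agrees with 0.029. Using 0.029 at both looks spends 0.0494 overall at t = 0.5 and 0.0467 at t = 0.625.
- Detectable difference: with 24 per arm, two-sided 0.05 and 80% power, the noncentral t gives 0.826 SD, which agrees with 0.83.

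**2. Power of the final test alone.** df = 46 and noncentrality = 0.826 × √(24/2) = 2.861.
- At 0.05 (critical t = 2.013): 80.0%.
- At 0.029 (critical t = 2.254): 72.7%.

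With 0.83 in place of 0.826 the figures are 80.4% and 73.1%.

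**3. Power if rejection at either look counts.** I simulated 1,000,000 two-look t-test trials (15, then 24 per arm, 0.029 at each look) at 0.826 SD. Overall power is 75.2%, the chance of crossing at the interim is 49%, and type I error is 0.047. The normal approximation gives 75.4% (t = 0.5) to 75.7% (t = 0.625), with a 42% to 51% chance of crossing at the interim.

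**4. Sensitivity to the effect size.**

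| True difference | One test at 0.05 | Final test at 0.029 only | 0.029 at either look |
|---|---|---|---|
| 0.826 SD | 80.0% | 72.7% | 75.2% |
| 0.5 SD | 39.6% | 31.0% | 34.8% |
| 5 mL, SD 7.0 (5/7.0 = 0.71 SD) | 67.8% | 59.0% | not run |
| 5 mL, SD 13.2 (5/13.2 = 0.38 SD) | 25.0% | 18.3% | not run |

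The plan states the 5 mL target for full against empty breasts, so the last two rows only show the loss on that scale.

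**5. What an interim crossing would look like.** At 0.029 the critical t on 28 df is 2.302, so the observed gap must reach 2.302 × √(2/15) = 0.84 SD. If the true gap is 0.5 SD, favourable crossings average about 1.00 SD.

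**6. A stricter boundary, 0.005 interim and 0.048 final.** Overall type I error is 0.0499 at t = 0.5 and 0.0492 at t = 0.625. Overall power is 79.5% at 0.826 SD and 80.0% at 0.83 SD. The chance of crossing at the interim falls from 49% to 24%. The gap needed is 3.047 × √(2/15) = 1.11 SD, and at a true 0.5 SD favourable crossings average about 1.17 SD.

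**The case against.** The strongest reply is that a Pocock level set at an interim is by construction an early-rejection boundary. The plan also states that the look is for efficacy as well as safety. A reader might infer from the safety-only termination rule that the efficacy look serves no purpose and returns nothing. The documents do not support that. If crossing counts as rejection, about 2.5 points of power come back (72.7% to 75.2%), along with roughly an even chance of an early answer at 0.83 SD. What survives is narrower: the boundary exists as a number, and its consequence is not written down.

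A reader might also link the look to biased measurement, because the protocol says "On occasion the CPI may be the assigned neonatologist responsible for the medical care of study participants". The next sentence of *Ethics* keeps that investigator out of recruitment and data collection, and no section says who will see interim results. The point does not rest on this.

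Three further replies have some force:
- The 0.83 SD is stated for secondary outcomes, and the plan expects its mixed models to be more powerful than the t-test. The power figures are therefore illustrations, although a lower threshold costs power under any analysis.
- The drop from 80% to 73% is also what follows from sizing the trial at 0.05 and testing at 0.029. Re-sizing at 0.029 would need 28 analysable infants per arm, or 28/0.8 = 35 recruited, and would still leave the interim action unstated.
- Exaggeration after early crossing belongs to all early stopping, and a stricter boundary makes it worse, as step 6 shows. It is not a special fault of this plan.

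**Conclusion.** The point holds as an omission with a measurable cost. The plan tests the primary endpoint at 15 infants per arm, lowers the final threshold to 0.029 on that account, and never says what an efficacy crossing means. On the planning t-test with 24 per arm and about 0.83 SD, power falls from 80% to about 73% if a crossing has no consequence, and to about 75% if rejection at either look counts. The loss is therefore 5 to 7 points.

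This assumes two-sided tests and the plan's 20% dropout. If all 30 per arm were analysed at the same design effect, the normal approximation gives 87.9% at 0.05, against 82.9% (final test only) and 84.4% (either look). The 0.029 itself is a correct two-look Pocock value, and using it does not inflate the type I error. This is an inexpensive improvement to make before the trial starts; it does not invalidate the design.

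**What to change.** **Preferred.** In *Assessment of Efficacy* and *Statistical analysis*, make the interim review safety-only, state that breastfeed volume will not be compared between arms before the final analysis, and run the final primary analysis at two-sided 0.05. This recovers the 5 to 7 points without more infants and leaves safety monitoring as it is. The cost is wording, plus the loss of an early efficacy claim.

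**If an efficacy look is wanted.** State in *Criteria for termination of the trial* and in *Statistical analysis* what decision follows an interim crossing, and use a strict interim boundary. For example, 0.005 interim and 0.048 final keeps overall power at about 80% with type I error just under 0.05. The cost is that early crossing becomes rarer (about 24% against 49% at 0.826 SD) and the estimate at an early crossing more exaggerated (about 1.17 SD against 1.00 SD when the truth is 0.5 SD).

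**Under either option.** State that the test is two-sided. Reconcile the timing of the interim: the termination section places it at recruitment of 15 per arm, while the efficacy, safety and statistical sections wait for complete data on 15 per group.
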